# Subcutaneous tunnelling versus conventional insertion of peripherally inserted central catheters in hospitalized patients (TUNNEL-PICC): a study protocol for a randomized controlled trial

**DOI:** 10.1186/s13063-022-06682-2

**Published:** 2022-09-15

**Keywords:** Peripherally inserted central venous catheter, Central venous catheterization, Central line-associated bloodstream infections, Catheter-related bloodstream infections

## Abstract

**Background:**

Peripherally inserted central catheters (PICCs) are now widely used in modern medicine, and associated complications have also increased. Central line-associated bloodstream infection (CLABSI) is the most serious complication because it can cause extended hospital stays and increase costs. Furthermore, it can contribute to dire consequences for critically ill patients. Subcutaneous tunnelling for central venous catheters is an accepted method to reduce the risk of CLABSI. However, it is not generally adopted for PICC placement in most hospitals because its safety and efficacy have not been thoroughly evaluated.

**Methods:**

In this multi-institutional, prospective, non-blinded pragmatic randomized controlled trial, 1694 patients treated at five referral hospitals will be assigned to one of two parallel arms (conventional and tunnelled PICC groups) using computer-generated stratified randomization. The conventional group will undergo PICC placement by routine practice. In the tunnelled PICC (tPICC) group, additional subcutaneous tunnelling will be applied. Patients will be followed until PICC removal or the end of this study. The primary endpoint is whether subcutaneous tunnelling reduced the rate of CLABSI compared to the conventional method. The secondary endpoints are technical success rates, complications including exit-site bleeding or infection, and the procedure time between the groups.

**Discussion:**

Subcutaneous tunnelling is a widely used method to reduce catheter-associated infection. However, it has not been thoroughly applied for PICC. A randomized trial is needed to objectively assess the effects of the subcutaneous tunnel in PICC placement. This TUNNEL-PICC trial will provide evidence for the effectiveness of subcutaneous tunnelling in decreasing the risk of CLABSI.

**Trial registration:**

Clinical Research Information Service (CRiS) KCT0005521

## Administrative information

Note: the numbers in curly brackets in this protocol refer to SPIRIT checklist item numbers. The order of items has been modified to group similar items (see http://www.equator-network.org/reporting-guidelines/spirit-2013-statement-defining-standard-protocol-items-for-clinical-trials/).

## Introduction

### Background and rationale {6a}

Intravenous catheterization plays a pivotal role in patient care in modern medicine. Over the past decade, the use of peripherally inserted central venous catheters (PICCs) has continuously increased due to their advantages over other central venous catheters. They can centrally infuse vesicant or irritant agents from safe peripheral access. They are also versatile, easy to insert, and carry a relatively low rate of infection [1, 2]. However, PICC-associated bloodstream infections have been reported at rates of 0.6–7.4% and are as frequent as non-tunnelled central venous catheters [1, 3–8]. Central line-associated bloodstream infection (CLABSI) often requires intravenous antibiotic therapy, prolonged hospitalization, and even mortality in critically ill patients [9]. Traditionally, subcutaneous tunnelling has been used for central venous catheter placement (i.e. cuffed-tunnelled haemodialysis catheter, Apheresis catheter, or implantable venous port) [10]. Although subcutaneous tunnelling effectively reduces catheter-related infection, it has not been frequently used in PICC insertion, except for paediatric central line placement [11]. In 2001, Selby et al. reported the technical feasibility and safety of subcutaneous tunnelling on PICC insertion [12]. In addition, a bi-centre retrospective study demonstrated the protective effect of subcutaneous tunnelling on PICC-associated CLABSI [13]. However, no randomized controlled trial has compared the impact of subcutaneous tunnelling-applied PICC (tPICC) versus conventional PICC (cPICC) insertion with a focus on CLABSI. We hypothesized that using the subcutaneous tunnel for PICC insertion would effectively reduce the infection rate, even without tunnel-dedicated devices. This multi-institutional, open-label, parallel-group, pragmatic, randomized controlled trial study is designed to compare the catheter-related bloodstream infection rates of tPICC and cPICC in hospitalized patients.

### Objectives {7}

The objective is to evaluate the effect of subcutaneous tunnelling in PICC placement on the rate of CLABSI.

### Trial design {8}

This trial will be a prospective, randomized, controlled, investigator-initiated, multi-institutional, open-blind superiority study in five referral hospitals in the Republic of Korea. The allocation will be a 1:1 ratio of two parallel groups.

## Methods: participants, interventions, and outcomes

### Study setting {9}

This multi-institutional randomized controlled trial will be performed in five hospitals located in the metropolitan city of Korea: (1) Ajou University Hospital, (2) Hanyang University Guri Hospital, (3) Ewha Women’s University Seoul Hospital, (4) Seoul National University Bundang Hospital, and (5) Incheon St. Mary’s Hospital, Catholic University of Korea. All five hospitals are regional referral and educational institutions with more than 530 beds and can provide services to in- and outpatients. In addition, Seoul National University Bundang Hospital is a public hospital, and private academic foundations run other hospitals.

### Eligibility criteria {10}

Eligible patients are >18 years of in-patients who require PICC insertion, according to the physician’s decision. Because the diagnosis of CLABSI requires at least 48 h of dwelling time, patients with pending discharge or transfer to another hospital within 2 days after catheterization will be excluded. In addition, this study will be pragmatic, and participants will not be excluded due to ongoing medical conditions, e.g. ongoing infection, malignancy, or immunity. Figure 1 shows the CONSORT flow chart of this study. Both tPICCs and cPICCs will be placed by one interventional radiologist at each institution designated for this study. Participants who will be treated on an outpatient base will be not included because infection-associated symptoms can be missed.

**Fig. 1 Fig1:**
[figure not shown]
The CONSORT flow chart of this study

### Who will take informed consent? {26a}

Mostly, it has taken a single-working day from PICC requests to implementation in all five hospitals. Informed consent will be obtained by investigators of each institution at least 1 day before PICC placement. In patients with urgent medical necessity, which the referring physician will decide, informed consent will be obtained within at least 6 h of the procedure. Investigators will provide information sheets to participants and a detailed explanation of the study before obtaining informed consent.

### Additional consent provisions for collection and use of participant data and biological specimens {26b}

Not applicable.

### Interventions

#### The explanation for the choice of comparators {6b}

We hypothesize that using the subcutaneous tunnel for PICC insertion will reduce the CLABSI rate compared to conventional methods.

#### Intervention description {11a}

Participants will be allocated into two groups. The cPICC group will have PICC placement with the traditional method under ultrasonography and fluoroscopic guidance in an angiography suite. Procedures will be implemented under hand hygiene, maximal sterile barrier, and chlorhexidine. The targeted arm will be sterilized with a mixture of chlorhexidine and isopropyl alcohol, and a sterile drape will be placed to cover the entire procedure field from head to toe [14]. A 5-French, dual lumen PICC from a vendor will be used (UNIS; Genoss Co., Gyeonggi-do, Korea). The tPICC group will undergo PICC placement in the same manner and place with additional subcutaneous tunnelling. Most commercially available PICCs contain no tunnellers or Dacron cuffs. Thus, after vein puncture with the access needle, a Nitinol guidewire will be placed as usual. We will make a tunnel 2–3 cm distal to the initial venepuncture site using an additional 18-gauge needle, and the guidewire will be retrogradely passed through the needle. After resolution of the loop over the venepuncture site, a peel-away sheath will be placed over the wire. The catheter will be trimmed to the distance between the venepuncture site and cavoatrial junction plus the subcutaneous tunnel before being inserted in the usual manner. The initial venepuncture and exit-site wounds will be closed by applying a small amount of *n*-butyl-2-cyanoacrylate (Fig. 2).

**Fig. 2 Fig2:**
[figure not shown]
**A** Subcutaneous tunnel creation while placing a peripherally inserted central catheter (PICC). First, venepuncture under ultrasonography guidance will be performed with a puncture needle included in the PICC set, and a guidewire will be placed at an upper arm vein. Then, a subcutaneous tunnel will be created with an 18-gauge needle 1-inch away from the initial venepuncture site. **B** A guidewire will be passed through the needle under the subcutaneous tunnel. The loop will be resolved with a gentle snapping of the guidewire. **C** A peel-away sheath will be placed in the vein under the subcutaneous tunnel and over the guidewire. **D** Both wounds (initial venepuncture and catheter-exit sites) will be closed with glue (Histoacryl; B. Braun, Rubí, Spain)

#### Criteria for discontinuing or modifying allocated interventions {11b}

Patients who do not want to participate in the trial or accidentally lose the PICC within 48 h after the procedure will be excluded from the study. There are no criteria for modifying allocated intervention.

#### Strategies to improve adherence to interventions {11c}

This study includes one-time intervention during the procedure and is a pragmatic study. All procedures will be performed by interventional radiologists involved in this study. Investigators will share procedure details on tunnelling methods by a standard manual and workshops

#### Relevant concomitant care permitted or prohibited during the trial {11d}

Not applicable. This is a pragmatic study. After PICC insertion, participants will be treated by their disease course. Relevant concomitant care will not be provided nor prohibited during trial.

#### Provisions for post-trial care {30}

Subcutaneous tunnelling is a widely used central venous catheter placement procedure with no serious reported complications. However, investigators will try to attenuate any damage from the intervention. When it is impossible to recover from irreversible injury, an insurance program for this study will provide compensation. Patients will not be compensated for their participation in the study.

#### Outcomes {12}

The primary outcome is the effect of subcutaneous tunnelling in PICC placement on the rate of CLABSI. We will use the National Healthcare Safety Network surveillance definition [15]. CLABSI will be defined as a laboratory-confirmed bloodstream infection where the PICC is in place for more than 48 h and must meet both of these criteria: participants have a recognized pathogen identified from one or more blood specimens by culture- or non-culture-based microbiologic test, and organisms identified in the blood are not related to an infection at another origin (e.g. mucosal-barrier injury). A board-certified infection disease specialist will diagnose CLABSI at each institution, independent of this study for blinding.

The secondary outcomes include rates of local infection and bleeding from exit sites, extra procedure time for subcutaneous tunnelling, and technical success, defined as the rate of successful catheter tip placement to the cavoatrial junction. The local infection will be defined as one or combined symptoms followings: insertion site swelling with tenderness, local heating sense, or pus. Bleeding from exit sites will be marked when PICC cannot be kept in place due to continuous bleeding. Minor oozing causing dressing change will not be counted as this outcome. We will divide technical success into two categories. If there is a failure in puncturing the target vein or placing the catheter to the cavoatrial junction, we will define it as ‘impossible PICC.’ In case of subcutaneous tunnelling failure after target vein puncture, we will explain it as ‘impossible tunnelling.’

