### Sample size {14}

According to previous reports about PICC, infection rates range from 0.6 to 7.4% [1, 3–5]. In a previous retrospective study, the CLABSI rate of tPICC was 2.6% [13]. The sample size was calculated by assuming the same infection rate in this trial to verify the prior retrospective study result. In this trial, 2 × 677 participants are needed to prove a reduction of the infection rate from 6.2 to 2.6% for the primary outcome, at a two-sided α level of 0.05 and statistical power of 90%. A total of 1694 participants will be included in this study to account for a 20% dropout rate (PASS, version 16, NCSS statistical software). Data will be analysed on an intention-to-treat basis according to their originally assigned group.

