### Data collection and management

#### Plans for assessment and collection of outcomes {18a}

In line with the pragmatic study, the participants will be treated for their condition according to the initial treatment plan. Daily physical examination and laboratory tests will be performed on a treatment schedule. Blood culture and laboratory testing will be performed as usual management when the participants have a symptom or sign of infection. Laboratory tests include white blood cell count with differentiation, erythrocyte sedimentation rate, and C-reactive protein level.

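### The written CLABSI rule has no route for common skin commensals, and the protocol does not say whether that rule or the surveillance definition it cites governs

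*Protocol article*

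**What the plan says.** The Outcomes section {12} of the protocol article opens the endpoint definition with a citation: "We will use the National Healthcare Safety Network surveillance definition [15". It then writes out a rule. The PICC must have been in place for more than 48 h, and the bloodstream infection "must meet both of these criteria". The first criterion is that "participants have a recognized pathogen identified from one or more blood specimens by culture- or non-culture-based microbiologic test". The second is that "organisms identified in the blood are not related to an infection at another origin (e.g. mucosal-barrier injury").

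On who decides, the same section says: "A board-certified infection disease specialist will diagnose CLABSI at each institution, independent of this study for blinding". On how blood is obtained, the assessment section {18a} says: "Blood culture and laboratory testing will be performed as usual management when the participants have a symptom or sign of infection".

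The sample size section {14} says that "2 × 677 participants are needed to prove a reduction of the infection rate from 6.2 to 2.6% for the primary outcome". The significance level behind this is 5%, two-sided, and the power is 90%. A 20% dropout allowance brings the total to 1694.

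The article does not define a recognized pathogen. It does not mention skin commensals, matching repeat cultures, or a sign of infection as part of the case definition.

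**The concern.** The rule is closed. Both criteria are compulsory, and the first names one class of organism with no alternative.

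Take a patient with a PICC in place for nine days, fever, the same coagulase-negative staphylococcus in two separately drawn blood cultures, and no other source. An assessor who follows the written criteria can say that a skin commensal is not a recognized pathogen and record no CLABSI. An assessor who goes to the cited definition may decide otherwise, depending on what that source says about commensals. The article gives no order of precedence. Diagnosis is made separately at each of five hospitals, and no central review is described.

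This rule decides which patients count as primary events. If a class of genuine catheter infections is left out, the trial has fewer events than it could have. If some hospitals leave it out and others do not, the endpoint means different things at different sites.

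**Working it through.** **The text, step by step**

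1. The citation sentence alone would import the whole external definition, including whatever it says on commensals.
2. The sentences after it state a rule that must be met in full. Its microbiological element covers recognized pathogens only.
3. The one-specimen threshold belongs to that element, so it applies to recognized pathogens and to nothing else.
4. No sentence ranks step 1 against step 2. Taken literally, step 2 excludes a commensal infection however many cultures agree.
5. Cultures are drawn in usual care, so the number of specimens per patient is not fixed. Any criterion based on repeat cultures must work with what was drawn.

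**The plan's own figure**

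Inputs from Sample size {14}: p1 = 0.062, p2 = 0.026, two-sided α = 0.05, power 0.90.

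Unpooled normal approximation: n = (1.960 + 1.282)² × [p1(1 − p1) + p2(1 − p2)] / (p1 − p2)² = 10.507 × (0.058156 + 0.025324) / 0.001296 = 676.8, so 677 per arm. Then 677 / 0.80 = 846.25, so 847 per arm and 1694 in total. Both stated figures reproduce, so there is no arithmetic error.

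**Illustration of lost events**

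Two assumptions are added, neither taken from the documents:
- The planning rates include commensal infections.
- A fraction f of events is of that kind and is lost equally in both arms, with f from 20% to 40%.

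Power = Φ{[(p1 − p2) − 1.960 × SE0] / SE1}, where SE0 = √[2p̄(1 − p̄)/n], p̄ is the mean of the two rates, and SE1 = √{[p1(1 − p1) + p2(1 − p2)]/n}.

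Worked case, f = 0 and n = 677: SE0 = 0.01115, SE1 = 0.01110, (0.036 − 0.02185)/0.01110 = 1.27, power 89.9%.

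| f lost | Rates, conventional vs tunnelled | Power, n = 677 | Power, n = 847 |
|---|---|---|---|
| 0 | 6.20% vs 2.60% | 89.9% | 95.1% |
| 20% | 4.96% vs 2.08% | 82.1% | 89.6% |
| 40% | 3.72% vs 1.56% | 69.8% | 79.2% |

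At 677 per arm the expected total falls from 59.6 events (42.0 + 17.6) to 47.7 at f = 20% and 35.7 at f = 40%. The risk ratio stays at 0.026/0.062 = 0.42 in every row, because the loss is proportional by construction. The illustration therefore shows loss of precision, not bias.

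**The case against.** The strongest defence is the citation. The section adopts a full surveillance definition before it lists its criteria, and a journal article condenses. The two criteria may be a short paraphrase, with the detailed organism rules in the full protocol (version 1.4, under Trial status) and already applied by the specialists. The cited source is not at hand, so its treatment of commensals cannot be checked. This stands in part: it cannot be claimed that commensal infections are in fact being dropped. It does not dispose of the point, because the article goes beyond omitting detail. It states a compulsory test that is narrow as written and leaves the order of precedence open.

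The power figures are also open to challenge, and that challenge stands. The sample size section ties its assumption to a prior retrospective study whose case definition is not reproduced. If that study counted cases by the same narrow rule, no planned power is lost. The 20-40% share has no source in the documents, and 677 per arm supposes that the whole dropout allowance is used up.

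A reader might go further and infer three things that the documents do not support:
- **Single-bottle contaminants will be counted.** One specimen suffices only for a recognized pathogen. Counting a lone commensal needs an assessor to stretch that term against its plain meaning.
- **The arms are biased against each other.** The section on who will be blinded {17a} says that outcome assessors are blinded to allocation and cannot see the assignment form. Nothing shows error that differs by arm.
- **The loss falls on exactly the infections a tunnel prevents.** No section gives organism data or says that tunnelling acts mainly on skin commensals.

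**Conclusion.** The point holds as a defect in how the primary endpoint is written. The rule, followed literally, excludes commensal catheter infections even when repeat cultures agree and no other source exists, and the article does not say whether the citation overrides it. The consequence is a risk of lost events and of inconsistent coding across five hospitals. The documents do not show that any patient has been misclassified.

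The size is conditional. Power would be about 82-70% at 677 per arm, or about 90-79% at 847, if 20-40% of the planned events were commensal infections and were lost equally in both arms. If the planning rates never included such infections, or if assessors already apply the full cited definition, the loss is smaller or absent. The figures illustrate why the wording matters and are not an estimate of harm. The case for correcting the text does not depend on them.

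**What to change.** State in Outcomes {12} that the full cited definition governs, and write the microbiological criterion as two alternatives:

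- (a) a recognized pathogen in at least one blood specimen; or
- (b) the same common commensal in at least two blood specimens drawn on separate occasions, plus a recorded sign of infection.

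Add that a commensal in a single specimen is not an event. Keep the 48 h and no-other-source conditions for both routes. Check the final wording against the cited source, so that text and citation agree.

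For patients already enrolled (700 at manuscript submission), have the blinded assessors check the existing culture reports and re-code only those classified under the narrower rule. Do this before the data analysts are unblinded. No interim analysis is planned, so the change can be made without sight of results by arm.

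The cost is a wording amendment, notified to each ethics board and the registry as the protocol already provides, and a review of existing reports. No new samples are needed. There is one small downside: because cultures follow usual care, a patient with a commensal in the only culture set drawn cannot qualify.

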### Participant timeline {13}

**Table Tabb:** 

Timepoint**	Study period			
	Enrolment	Allocation	Post-allocation	Close-out
	***− 1–3 days***	0	***Until catheter removal or hospital discharge***	***After catheter removal or hospital discharge***

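### The local-infection outcome does not separate infection from reaction to the procedure, so any excess site reaction caused by tunnelling would count against tPICC

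*Protocol article*

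**What the plan says.** Outcomes {12} lists local infection first among the secondary outcomes: "The secondary outcomes include rates of local infection and bleeding from exit sites". It is defined as "one or combined symptoms followings: insertion site swelling with tenderness, local heating sense, or pus". Any one of the three items is enough. No onset time, persistence, culture, treatment or clinician diagnosis is attached.

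The two neighbouring outcomes in that section do carry a filter. CLABSI is a "laboratory-confirmed bloodstream infection where the PICC is in place for more than 48 h", with further microbiological conditions. For exit-site bleeding, "Minor oozing causing dressing change will not be counted as this outcome".

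Intervention description {11a} gives the tunnelled arm an extra step: "We will make a tunnel 2–3 cm distal to the initial venepuncture site using an additional 18-gauge needle". It also implies two separate wounds in that arm: "The initial venepuncture and exit-site wounds will be closed by applying a small amount of" tissue glue.

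In Participant timeline {13} the post-allocation period runs "Until catheter removal or hospital discharge", and no early part of it is set aside. Statistical methods {20a} plans a hazard ratio with a 95% confidence interval for each complication.

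**The concern.** Pus points to infection. Swelling with tenderness, and a feeling of heat, may be infection or may be the tissue's response to a needle and catheter. The rule cannot tell these apart, and it applies from the moment of insertion, when a procedural response is most likely.

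This would matter little if both arms had the same procedure, but they do not. If the tunnel causes more early swelling, tenderness or heat than a conventional insertion does, the excess enters the tPICC count as infection. The misclassification then differs by arm. The trial could report that tunnelling raises local infection when it only causes short-lived soreness, or a true reduction could be cancelled out. Local infection is one of few safety comparisons in the trial, and its label is close to the trial's central question.

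**Working it through.** **1. The plan's own figure.** Sample size {14} gives 677 per arm for CLABSI of 6.2% against 2.6%, two-sided α 0.05 and 90% power. With unpooled variance:

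n = (1.960 + 1.282)² × (0.062×0.938 + 0.026×0.974) / 0.036² = 676.8, so 677.

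Allowing for 20% dropout, 677/0.80 = 846.25, so 847 per arm and 1694 in total. Both figures reproduce. They rest on CLABSI alone, so nothing below changes them.

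**2. Does anything else in the article remove the problem?**
- Criteria for discontinuing {11b} has a 48 h rule, but it removes patients who withdraw or lose the catheter early. It does not remove early local signs.
- Blinding {17a} says outcome assessors are blinded. A blinded assessor applying this wording would still count a reaction that meets it.
- The independent infectious disease specialist in Outcomes {12} diagnoses CLABSI only.
- Participant timeline {13} lists procedure-associated and delayed complications separately but assigns local infection to neither.

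**3. How large could the effect be?** The article gives no rate for local infection or site reaction, so both are assumptions. Let b be the true local-infection risk in both arms and e the excess risk in tPICC from reactions that meet the definition. The observed risks are then b and b + e, with n = 677 per arm.

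- Pooled standard error: SE₀ = √[2·p̄(1−p̄)/n], where p̄ = b + e/2.
- Unpooled standard error: SE₁ = √[(b(1−b) + (b+e)(1−b−e))/n].
- Chance of p<0.05: Φ[(e − 1.96·SE₀)/SE₁] + Φ[(−e − 1.96·SE₀)/SE₁].

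For b = 3% and e = 1%: SE₀ = 0.00999 and SE₁ = 0.00998. The first term is Φ(−0.96) = 0.169 and the second is 0.0015, giving 0.17.

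| Excess e (b = 3%) | Apparent risk ratio | Chance of p<0.05 |
|---|---|---|
| 0 | 1.00 | 5% (nominal) |
| 0.5% | 1.17 | 8% |
| 1% | 1.33 | 17% |
| 2% | 1.67 | 47% |
| 3% | 2.00 | 76% |

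A lower assumed base rate makes the same excess more visible. At e = 1% the chance is 22% for b = 2% and 33% for b = 1%.

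**4. Masking.** Suppose tunnelling truly halves local infection from 2% to 1%, and a further 1% of tPICC patients have a qualifying reaction. The observed risks are 2% and 1% + 1% = 2%, a ratio of 1.0, and the benefit disappears.

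**The case against.** Several counter-arguments have force.

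- **The definition is not as loose as it may look.** A reader might infer that any one non-specific sign suffices. The first item already needs swelling and tenderness together, and pus is specific. Heat is the only lone non-specific sign. This stands, although swelling with tenderness can still be procedural.
- **The arms are less different than a bare contrast suggests.** A reader might infer that a tender track on day 1 is plainly a local infection in tPICC and has no counterpart in the other arm. The article does not support that. The rule refers to the insertion site without saying whether this includes the tunnel or both wounds. Conventional insertion also involves a puncture, and Blinding {17a} notes that it can involve several incisions. Only the excess biases the comparison.
- **The CLABSI 48 h condition does not carry over.** It belongs to a bloodstream-infection surveillance definition. Nothing in the article says that site reactions end by then, so any cut-off here is a choice.
- **Detail may sit in the full protocol.** Onset recording could be there. But the article states an operative rule, and that rule as stated is the difficulty.
- **A sensitive harm definition can be defended.** It errs against the experimental arm in a pragmatic trial. This is a fair reason to keep the definition, but not to leave it as the only analysis, since the same error can hide a benefit.
- **Redefining mid-trial is costly.** Trial status reports 700 patients already recruited, and operators know the allocation. A stricter rule such as two of three signs after 48 h would also still count a swollen, tender site first seen on day 3. Both points weigh against replacing the definition.

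**Conclusion.** The point holds in a limited form. As worded, the outcome can count a procedural reaction as infection at any time after insertion. Because the extra needle pass and tunnel occur in one arm only, any excess reaction biases the comparison against tPICC. Nothing else in the article corrects this.

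The direction follows from the design, but the size does not. It depends entirely on two assumed rates, and with an excess of 0.5% or less the effect is slight. A reader might infer that the trial will produce a false safety signal, or that the main result is compromised. The article supports neither reading: how often tunnel reactions meet the definition is unknown, and the primary outcome does not use these signs. The consequence is confined to how a secondary result on local infection can be interpreted.

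**What to change.** Keep the stated definition as the main analysis of this outcome and make four additions:

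1. State that in tPICC the definition covers both the venepuncture and the exit site.
2. Record on the e-CRF, identically in both arms, which sign was present, at which site, and its onset date. The planned hazard ratios already need event times.
3. Before unblinding, pre-specify two further between-arm comparisons: one restricted to pus, and one restricted to onset after an early window (48 h is an example, to be justified by the investigators). Report earlier non-purulent signs separately as site reactions.
4. Conclude that tunnelling raises or lowers local infection only if the stated definition and the two restricted analyses agree.

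Cost: a short amendment and a few e-CRF fields. For the roughly 700 patients already enrolled at submission, sign and onset must come from source records and will be incomplete where those are silent. The restricted analyses will have fewer events. Even at an assumed 3%, the full definition yields only about 20 per arm (0.03 × 677), so the restricted estimates will be imprecise and serve mainly as a check on direction.
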